
### Monitoring

The current trial will utilise a Trial Management Group to supervise the overall conduct and safety of the trial in accordance with the National Health and Medical Research Council (NHMRC) guidelines on Data Safety Monitoring [92]. Details about this group are published on the Australian New Zealand Clinical Trials Registry (see here). As this trial includes symptomatic adolescents, each study assessment will include a list of mental health services and support resources suitable for adolescents. Participants who report an Adverse Event (AE), which includes severe suicide ideation (indicated by a score of ≥2 on item-9 of the PHQ-A) reported at baseline or the primary or secondary end-points and severe depressive symptoms (indicated by a total score ≥ 20 on the PHQ-9-A) reported at the secondary endpoint, will be offered a follow-up call from a Clinical Psychologist who will conduct a risk assessment over the phone. If at risk, the participant will be advised to contact an appropriate service. Parents will be contacted if the risk of harm is deemed imminent or the participant requests it. All adverse events and serious adverse events will be formally recorded and reported to the Trial Management Group in a monthly report and to the University of New South Wales Human Research Ethics Committee by the Clinical Trial Manager. No interim analyses on primary or secondary outcomes are planned, unless it is warranted by safety reports or upon the request of the Trial Management Group. The Trial Management Group may recommend pausing or terminating the trial if they have concerns for participant safety, based on (but not limited to) a higher than anticipated rate of one or more of the primary endpoints. At any time, the University of New South Wales can audit trial conduct and this process will be independent from the investigators and the sponsor.

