**Methods:**

We aim to recruit 489 adolescents aged 12-17 years with mild to moderately-severe depressive symptoms. Participants will be screened for inclusion, complete the baseline assessment and are then randomly allocated to receive ClearlyMe® (self-directed use), ClearlyMe® with guided SMS support (guided use) or digital psychoeducation (attention-matched control). Depressive symptoms and secondary outcomes will be assessed at 6-weeks (primary endpoint) and 4-months post-baseline (secondary endpoint). Engagement, conceptualised as uptake, adherence and completion, will also be assessed 6-weeks post-baseline. Mixed-effects linear modelling will be used to conduct intention-to-treat analyses to determine whether reductions in depressive symptoms and secondary outcomes are greater for conditions receiving ClearlyMe® relative to control at 6-weeks and 4-months post-baseline and greater for intervention adherers relative to non-adherers. To minimise risk, participants will be encouraged to use the Get Help section of the app and can also opt to receive a call from the team clinical psychologist at baseline, and at the 6-week and 4-month post-baseline assessments when reporting suicidal ideation.

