## Methods/design

### Trial design

This superiority trial will utilise a three-arm, parallel group randomised controlled trial design with an equal allocation ratio. Outcome measures will be assessed at baseline, post-intervention (primary endpoint, measured at 6-weeks post-baseline) and follow-up (secondary endpoint, measured at 4-months post-baseline). A 4-month follow-up was selected to ensure participants in the control condition were provided with the intervention after a reasonable duration and to reduce participant attrition. The University of New South Wales is the sponsor of this clinical trial and ethics approval was given by the University of New South Wales Human Research Ethics Committee (HC#210889). This trial was registered with the Australian New Zealand Clinical Trials Registry on the 27th of January 2022 (ACTRN12622000131752) and has been allocated the Universal Trial Number U1111-1271-8519.

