### Participants

Eligible adolescents are those aged 12 to 17 years old; located in Australia; who own or have access to a smartphone; have access to the Internet, an active email address and mobile phone number; comfortable with reading English at Grade 7-8 level; and who can obtain their parent or guardian’s consent. Eligible adolescents must also report mild to moderately-severe depressive symptoms as determined by a total score ranging between 5 and 19 on the Patient Health Questionnaire for Adolescents (PHQ-A) at screening. Ineligible adolescents are those who are currently receiving or about to start psychological treatment from a mental health professional for symptoms of depression or anxiety; are currently taking or about to start a course of prescribed medication for symptoms of depression or anxiety; report severe suicidal ideation as determined by a score of ≥2 on item 9 of the PHQ-A; respond ‘yes’ to items asking whether within the past month they have had serious thoughts or intentions about ending their life, or have made an attempt to end their life; nil or severe depressive symptoms as determined by a total score of ≤4 or ≥ 20 on the PHQ-A; or fail to satisfy any of the inclusion criteria at screening. Uptake of other depression interventions during the trial is permitted and will be assessed at primary and secondary endpoints.

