### Interventions

Participants allocated to the intervention conditions (i.e., self-directed use of ClearlyMe® and guided use of ClearlyMe®) will be instructed to complete the ClearlyMe® app content by undertaking at least one collection per week (approximately 20 minutes in duration) for 6 weeks; however, participants can complete the app content in any order and according to their preferences. Participants will also be instructed to use the ‘Get Help’ section of the ClearlyMe® app if they feel they require extra mental health support during the intervention period, although this is not monitored by the research team. To promote compliance, participants allocated to this condition will be sent weekly SMS reminders (total of 6) to use the app. The ClearlyMe® app also includes an in-built ‘revisit the app’ reminder, which notifies participants to use the app after 7 days of inactivity. Participants who allow notifications during the app’s onboarding will receive these reminders but can deactivate it at any time via their mobile phone settings. Participants who fail to download the ClearlyMe® app within 7 days of randomisation will be sent one email and one SMS reminder to download the app. Participants who do not download the app will remain in the trial and be included in the intention to treat analyses.

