Participants in the Guided use of ClearlyMe® condition will also receive a weekly guided support session delivered outside of school hours via Short Message Service (SMS) by a member of the research team using a standard script and decision flow chart (see Additional File 1). Research Assistants (RAs) will be trained to conduct these sessions and will be supervised by an experienced clinical psychologist. These sessions will consist primarily of technical support with some low intensity motivational coaching to encourage app use. The chat sessions are designed to take place in one sitting (i.e., approximately 20 minutes) but given the nature of SMS communication, will occur until the script is completed. Duration and script compliance will be recorded. Chat sessions will be prescheduled to take place between 3:30 pm and 6 pm on Mondays to Fridays. For non-responsive participants, the research team will instigate one additional contact attempt, made within 2 days of the initial attempt, however, the weekly chat schedule will remain unchanged, regardless of when a participant responds. Participants in this condition will be provided an additional $25 reimbursement for phone credit upon allocation to the guided support condition.

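### A PHQ-A total of 20 or more is a named adverse event and prompts a psychologist call at 4 months, but not at the 6-week primary endpoint, and no reason is given

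*Protocol article*

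**What the plan says.** The Monitoring section of the protocol article defines, in one sentence, which reported scores count as adverse events and lead to the offer of a telephone risk assessment by a clinical psychologist. It gives each trigger its own time points:

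- Ideation: "severe suicide ideation (indicated by a score of ≥2 on item-9 of the PHQ-A) reported at baseline or the primary or secondary end-points".
- Total score: "severe depressive symptoms (indicated by a total score ≥ 20 on the PHQ-9-A) reported at the secondary endpoint".

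Trial design fixes the meaning of the second: "follow-up (secondary endpoint, measured at 4-months post-baseline", with the primary endpoint at 6 weeks. The Methods paragraph of the abstract also describes the call, tied to ideation alone: participants can opt to "receive a call from the team clinical psychologist at baseline, and at the 6-week and 4-month post-baseline assessments when reporting suicidal ideation".

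Under Participants, the same threshold is an exclusion at screening: "nil or severe depressive symptoms as determined by a total score of ≤4 or ≥ 20 on the PHQ-A". Under Outcomes, the PHQ-A total is the primary outcome, and under Procedure and participant timeline every randomised participant is invited to the 6-week assessment. The total is therefore collected at the visit where it triggers nothing.

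The general safeguards are a service list ("each study assessment will include a list of mental health services and support resources suitable for adolescents"), a Get Help section in the app or study site, and an encouragement, under Recruitment, to contact the team if distressed.

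**The concern.** The rule treats an identical score differently at two visits without explanation. Everyone enters with a screening total of 5 to 19, so a total of 20 or more at 6 weeks means that the adolescent has moved, since screening, into a band judged unsuitable for entry. Entry also excludes those receiving or about to start psychological treatment or medication for depression or anxiety, so no such care is in place at the outset. Treatment may be taken up later, but nothing in the protocol ensures it.

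Six weeks is an awkward visit to leave out. It closes the instructed use period and is the primary endpoint. Adverse events go to the Trial Management Group each month and to the ethics committee. As written, worsening into the severe band by the end of the intervention is not a named event in that reporting, although the Discussion says the evaluation is meant to establish safety as well as effectiveness.

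**Working it through.** The protocol states no figure on this point that could be reproduced. The check sets the rule out by visit, asks whether the gap can be reached, and then sizes it.

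**1. The rule by visit (Monitoring, Trial design)**

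| Visit | Item 9 ≥2 | Total ≥20 |
|---|---|---|
| Baseline | named | not named |
| 6 weeks (primary endpoint) | named | not named |
| 4 months (secondary endpoint) | named | named |

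**2. Can a participant score 20 or more without triggering the ideation rule?** The PHQ-A has nine items scored 0 to 3 (Outcomes). The eight items other than item 9 sum to at most 8 × 3 = 24.

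- Item 9 = 0: totals of 20 to 24 are reachable (other items summing to 20 to 24).
- Item 9 = 1: totals of 20 to 25 are reachable (other items summing to 19 to 24).

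Both lie in the severe band (20 to 27) and below the ideation threshold of 2. The abstract's looser wording about reporting suicidal ideation could cover item 9 = 1. It cannot cover item 9 = 0.

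**3. How far are entrants from the threshold?** From the top of the entry range, 20 − 19 = 1 point; from the bottom, 20 − 5 = 15 points.

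**4. How long until the next named check of the total?** Four months is 4 × 365.25 / 12 / 7 = 17.4 weeks, and 17.4 − 6 = 11.4 weeks.

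**5. How many adolescents?** Sample size gives 489 randomised and 20% attrition to the primary endpoint, so 489 × (1 − 0.20) = 391.2 expected completers. The document gives no proportion with a total of 20 or more and item 9 below 2. For an assumed share:

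- 1%: 391.2 × 0.01 = 3.9
- 5%: 391.2 × 0.05 = 19.6

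**6. Does another safeguard respond to the score?**

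- The service list goes to everyone at every assessment, whatever the score.
- Get Help relies on the adolescent; for the app, Interventions adds "although this is not monitored by the research team", and Control condition says much the same for the study site.
- Contacting the team when distressed also relies on the adolescent.
- The guided arm's weekly SMS contact is by supervised research assistants, but "These sessions will consist primarily of technical support with some low intensity motivational coaching to encourage app use". It belongs to the 6-week use period.
- Control participants have no further team contact unless they ask for technical support, apart from the adverse event calls that apply in all arms.

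None of these is prompted by a 6-week total of 20 or more.

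**The case against.** The strongest defence is that the difference may be deliberate. The call is a risk assessment, and the item that asks about suicidality triggers it at every visit. The total is the efficacy outcome, and a check on it at the last scheduled assessment fits a duty of care on exit. The article is also condensed, and it refers to a fuller preregistered plan and to ethics approval. That reading is possible, but the article does not state it. Because the sentence lists time points separately for each trigger, this is a rule as fixed, not detail left to another document.

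Second, a call at 6 weeks prompted by the primary outcome is a co-intervention before the 4-month endpoint. If the app works, more control participants would be called, which could narrow the 4-month contrast. This cost is real and should be acknowledged. It should be small: ideation calls already run at 6 weeks, and outside treatment is permitted. The call follows the 6-week measurement, so it cannot affect that participant's primary endpoint.

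Third, some crossings would be ordinary fluctuation, since a participant screened at 19 needs one point. That is fair, but it applies equally at 4 months, where the rule still acts.

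Fourth, the list of adverse events is open-ended, and the Trial Management Group can recommend pausing or stopping the trial. Neither tells staff to act on an individual 6-week score.

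Finally, adding 6 weeks still leaves baseline uncovered. Baseline may fall up to about two weeks after registration (one week for parental consent, then seven days), so a total of 20 or more is possible there too. This extends the fix and does not weaken the point.

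**Conclusion.** The concern holds. Followed as written, the protocol neither offers a call nor names an adverse event for a 6-week total of 20 to 24 with item 9 at 0. The same applies to totals of 20 to 25 with item 9 at 1, unless the abstract's looser wording is taken to govern. The gap to the next named check is about 11 weeks.

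The head count rests on an assumed 1% to 5% of 391 completers, or about 4 to 20 adolescents, and the conclusion does not depend on it. The estimand, type I error, power and the 6-week estimate are unaffected, and the 6-week scores remain on file. This is a safety rule that should be changed, or justified if it is intended. It may be a drafting slip, but the document does not say so.

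**What to change.** In Monitoring, amend the second trigger to read: *severe depressive symptoms (PHQ-A total ≥20) reported at the primary or secondary endpoint*. Run it through the psychologist call pathway already in use at 6 weeks for ideation. Consider adding baseline as well, since the total can rise between screening and baseline. If the restriction to 4 months is intended, state why.

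The cost is one phrase and no new data collection. At 6 weeks it adds about 4 to 20 call offers over the whole trial under the assumed 1% to 5%; baseline offers, if added, would come on top. The 4-month report should give the number of 6-week calls by arm, so that readers can judge any effect on that contrast.

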### Outcomes

#### Depressive symptoms

The primary outcome of this study is self-reported depressive symptoms as measured by the Patient Health Questionnaire-9 Adolescent version (PHQ-A) [44]. This 9-item self-report measure assesses the severity and frequency of depressive symptoms in the previous 14 days, with items rated on a 4-point Likert scale ranging from not at all (0) to nearly every day (3). Items are summed to produce a total score (range: 0 to 27) with higher scores indicating more severe depressive symptoms. Total scores will be used as the outcome measure, and can be classified into the following symptom severity categories: nil to minimal (0-4), mild (5-9), moderate (10-14), moderately severe (15-19), and severe (20-27). The PHQ-A is an adapted version of the validated PHQ-9 questionnaire [44, 45], has good psychometric properties for assessing depressive symptomology in adolescent populations [46–49] and has been endorsed for research and clinical evaluation with adolescents [44, 50, 51].

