#### Recent mental health care

At baseline participants will be asked to report whether they have ever been diagnosed with anxiety or depression by a health professional (yes - depression only, yes - anxiety only, yes -both depression and anxiety, no, I don’t know, I’d rather not say), whether they have ever received psychological treatment for a mental health problem or mental illness from a health professional (yes, no, I’d rather not say) and whether they have ever taken prescribed medication for a mental health problem or mental illness like depression or anxiety (yes, no, I’d rather not say). At the primary and secondary endpoints participants will be asked to report whether throughout the study they were diagnosed with depression or anxiety by a health professional (yes - depression only, yes - anxiety only, yes -both depression and anxiety, no, I don’t know, I’d rather not say), whether they received psychological treatment from a health professional (yes, no, I’d rather not say), starting taking prescribed medication for a mental health problem or mental illness (yes, no, I’d rather not say) or felt like they needed help for a mental health issue like depression or anxiety (yes, no, I’d rather not say).

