### Limitations

Due to its scale, this study will not conduct clinical interviews to yield a formal diagnosis of a mental disorder. However, measures with well documented psychometric properties that provide clinically relevant classifications of adolescent depressive symptomology and severity, which are frequently used in the literature for this purpose, have been selected [51]. Engagement with, and effectiveness of ClearlyMe®, will be examined in the controlled environment of a research trial providing little indication of how the app will be used in less controlled environments, such as in the community. Additional research examining the use of ClearlyMe® will be required to determine whether adolescents use the intervention differently in real-world settings [95]. The 4-month follow-up assessment will not allow for conclusions to be drawn about the long-term sustainability of the effects of ClearlyMe®. The incorporation of longer follow-up periods in future studies will be required. Instructions on how to use ClearlyMe® (i.e., at least 1 collection each week) were determined by predicting use that would produce optimal therapeutic benefit based on clinical experience. While this may not prove to be the optimal way to use ClearlyMe®, this trial will allow an examination of patterns of use associated with benefit. Finally, while the purpose of this first evaluation is to determine whether ClearlyMe® is effective and safe, subsequent evaluations could include an assessment of its cost effectiveness.

Notwithstanding these limitations, outcomes of this trial will provide valuable insights into the potential of a new CBT smartphone app to fill a gap in current treatment provision and factors driving and associated with therapeutic benefit.

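### Recording of all adverse events is promised and safety is a stated purpose, but after screening the only systematic suicidality enquiry described is PHQ-A item 9, whose recall covers about 23% of follow-up

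*Protocol article*

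**What the plan says.** The Monitoring section commits to full recording: "All adverse events and serious adverse events will be formally recorded and reported to the Trial Management Group in a monthly report", with the ethics committee as a second recipient. Under Limitations, the article says that "the purpose of this first evaluation is to determine whether ClearlyMe® is effective and safe".

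The suicidality trigger in Monitoring is "severe suicide ideation (indicated by a score of ≥2 on item-9 of the PHQ-A) reported at baseline or the primary or secondary end-points". The scale that contains item 9 "assesses the severity and frequency of depressive symptoms in the previous 14 days" (Outcomes, Depressive symptoms). After randomisation there are two assessments, at 6 weeks and at 4 months after baseline (Trial design).

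Separate yes/no items ask whether "within the past month they have had serious thoughts or intentions about ending their life, or have made an attempt to end their life". They appear under Participants, as exclusion criteria applied at screening.

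One set of follow-up questions does look back over the whole trial: "At the primary and secondary endpoints participants will be asked to report whether throughout the study they were diagnosed with depression or anxiety" (Recent mental health care). The same set covers psychological treatment, prescribed medication and felt need for help. No item on attempts, intent or self-harm is listed there.

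**The concern.** To record all adverse and serious adverse events, a trial needs a method of finding them. The participants are symptomatic 12- to 17-year-olds in a trial run wholly online, and attempts and serious suicidal intent are among the harms that matter most. The article describes whole-period recall for diagnosis, treatment and medication, but none for these harms.

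Two consequences follow. First, an episode that arises and eases between the recall windows, or an attempt at any time, need not appear in any scheduled measure described. A low count could then reflect the absence of a question rather than the absence of events. Second, the chance that such an event reaches the team depends on the arm, because staff contact between assessments depends on the arm. A between-arm comparison of events would mix a treatment effect with a difference in ascertainment. The Trial Management Group, which may recommend pausing the trial, would be working from the same counts.

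**Working it through.** The article gives no figure for how much of follow-up is covered by safety enquiry, so there is none to reproduce. Coverage can be computed from its own inputs.

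**Inputs**
- Follow-up assessments at 6 weeks (42 days) and 4 months (Trial design).
- PHQ-A recall of 14 days (Depressive symptoms).
- 4 months taken as 4 × 30.4375 = 121.75 days. This is an assumption and is varied below.
- 7 days allowed to complete each assessment (Procedure and participant timeline).

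**Share of follow-up inside the item 9 windows**
- Covered: 2 × 14 = 28 days; 28 / 121.75 = 23.0%.
- Outside: 1 − 28 / 121.75 = 77.0%.

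| Follow-up length | Share outside the windows |
|---|---|
| 112 days (16 weeks) | 75.0% |
| 120 days | 76.7% |
| 121.75 days | 77.0% |
| 123 days | 77.2% |
| 128.75 days (121.75 + 7) | 78.3% |

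**By segment, assessments on the nominal day**
- Baseline to 6 weeks: 42 − 14 = 28 days outside; 28 / 42 = 66.7%.
- 6 weeks to 4 months: 121.75 − 42 = 79.75 days, of which 79.75 − 14 = 65.75 are outside; 65.75 / 79.75 = 82.4%.

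**With missed assessments.** The Sample size section assumes 20% attrition by 6 weeks. If 20% also missed the 4-month assessment (an assumption; the article gives no figure for that time), the covered share would be (14 × 0.8 + 14 × 0.8) / 121.75 = 22.4 / 121.75 = 18.4%, leaving 81.6% of randomised person-time outside the windows.

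These figures concern ideation. Item 9 is described as a measure of suicidal ideation, and no post-screening item on attempts is described.

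**Routes between assessments, by arm**

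| Route | Guided | Self-directed | Control |
|---|---|---|---|
| Weekly SMS session with trained staff (Interventions) | Yes | Not described | No; no additional team contact unless technical support is requested (Control condition) |
| Participant contacts the team when distressed (Recruitment) | Yes | Yes | Yes |
| Use of Get Help monitored by the team (Interventions; Control condition) | No | No | No |

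The only route common to all arms is spontaneous. The only regular staff contact is in one arm, and its sessions are described as mainly technical support.

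**A related inconsistency in Monitoring.** Severe ideation counts as an adverse event at baseline and at both endpoints. Severe depressive symptoms (PHQ-A total of 20 or more) are named only at the secondary endpoint. No reason is given for the difference.

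**The case against.** The strongest objection is that this is a condensed article. Table 1, the assessment schedule, is not shown, and detailed elicitation forms and reporting timelines commonly sit in the full protocol. That stands as a limit on wording. A reader might infer that attempts are never asked about again, but the text supports only that no later item is described. It does not dispose of the point, because the article sets out its follow-up measures in detail, down to SMS feedback and programme barriers, and itself makes the unqualified statement about all events.

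A second objection is that other routes exist. The definition is open-ended, since it reads "Participants who report an Adverse Event (AE), which includes severe suicide ideation". Participants may contact the team, and guided-arm staff are in touch weekly under a clinical psychologist's supervision. So a reader who took 77% as the share of follow-up that is unobserved would go too far: it is the share outside item 9 recall. These routes are nevertheless passive or confined to one arm, and so cannot support a claim of completeness or a fair comparison.

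Three further inferences are tempting and unsupported:
- That nothing is asked of the 20% lost at 6 weeks. All randomised participants are invited again at 4 months.
- That a serious event must wait for the monthly report. The same sentence names the ethics committee as a recipient, and nothing makes the monthly report the only route.
- That the plan undertakes to show the app is safe. It says it will determine whether it is, in one sentence under Limitations. The objectives and hypotheses contain no safety objective, and no between-arm safety analysis is described.

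Nor do the documents give an event rate from which to predict how many events would be missed.

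**Conclusion.** The concern holds in a limited form. On the text shown, the described data collection does not support the statement that all adverse and serious adverse events will be recorded, nor a between-arm conclusion on safety. Systematic suicidality enquiry after randomisation reaches back over about 23% of the 4 months (22% to 25% across the follow-up lengths tried), and no systematic enquiry about attempts or serious intent is described after screening. Ascertainment between assessments differs by arm.

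This assumes that assessments fall on the nominal day, or within the 7-day window, and that Table 1 adds no such item. If the full schedule already contains one, the remedy is to say so. The primary efficacy estimate and its power are unaffected. This is a low-cost improvement to the safety evidence, worth making early because events that were not asked about cannot be reliably recovered later.

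**What to change.** 1. At 6 weeks and 4 months, repeat the existing yes/no screening items on serious thoughts or intentions and on attempts, with the recall period changed to since your last study assessment, worded identically in all three arms. Anchoring recall to the last assessment actually completed lets a participant who missed 6 weeks answer for the whole period at 4 months.
2. Base any between-arm safety comparison on these systematically collected items, and report spontaneously notified events separately, with the difference in staff contact stated.
3. If the items are not added, restrict the statements in Monitoring and Limitations to severe ideation and severe symptoms in the 14 days before each assessment, plus events reported spontaneously.
4. Reconcile the assessment times at which severe depressive symptoms and severe ideation count as adverse events in Monitoring.

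The cost of the first change is about a minute more per assessment, a minor ethics amendment and possibly some extra follow-up calls. The items already exist in the online screener. The other changes are to wording and analysis only.
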